### Trial Design

This study is a 2-arm randomized controlled trial (RCT) that will test the efficacy of a web-based adaptation of iJobs. Participants will be randomly assigned (1:1 allocation) to either the intervention group, which benefits from the iJobs program, or a waiting list control group that will also receive the iJobs intervention 2 weeks after the intervention group finishes it. The 2 independent groups (intervention vs waiting list control group) will be crossed with 3 measurement times (ie, baseline, the postintervention time point, and 1-month follow-up). Hence, the design will be a 2 (intervention vs control) × 3 (baseline, the postintervention time point, and 1-month follow-up) factorial design.

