##### About JSSE

The JSSE [18] will be used to assess participants’ perception of their ability to gain employment. The scale has 20 items (eg, “I believe my job search will be successful”) on a 5-point scale (1=a little; 5=a great deal), with a total score between 20 and 100. A higher score means a better outcome. JSSE will be measured at baseline, the postintervention time point, and follow-up.

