##### Sociodemographics

At baseline, participants will fill in their age, gender, residential area, educational level, average monthly income, unemployment period, work experience, and targeted professional field.

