### Statistical Analysis

#### Power

The sample size estimation in GPower (Heinrich-Heine-Universität Düsseldorf) for a mixed factorial design aiming for a .80 statistical power is 132 participants. Based on our previous results from a feasibility and acceptability trial on iJobs, we can anticipate a possible dropout rate of about 36% (n=48). Thus, the final sample aimed for enrollment will be 180 eligible participants (see Figure 3 for the flowchart).

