#### Data Analysis

We will use data from all the participants eligible for this study who completed the pretest measures. The data will be analyzed using the intent-to-treat framework with linear mixed model procedures. Intention-to-treat is based on the principle “once randomized, always analyzed.” It is a pragmatic approach to avoid bias in estimating the effect of treatment assignment in RCTs. We will use the linear mixed model approach without ad hoc imputations because it is more powerful than other options for studies with a high percentage of missing data [31].

For all the outcomes, time (baseline vs the postintervention time point) will be set as the within-group factor, and trial condition (intervention vs waiting list control group) will be used as the between-groups factor. We will analyze these 2 variables together with the entire set of outcomes (baseline vs postintervention comparison for the primary and secondary outcomes) to estimate the intervention’s effect size. Baseline to 1-month follow-up comparisons will be made to test how much the primary outcomes are preserved in time. We will also conduct separate analyses for each outcome with group, time, and group-by-time interaction as fixed effects and a random intercept for subjects with an identity covariance structure. The group-by-time interactions express the mean outcome change between the 2 trial groups from baseline to posttreatment.

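### The planned group-by-time test leaves the baseline group difference free and so gives up precision that adjusting for the collected baseline score would recover

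*Protocol article*

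**What the plan says.** The Data Analysis section places baseline inside the response: "time (baseline vs the postintervention time point) will be set as the within-group factor". The model for each outcome is then stated: "We will also conduct separate analyses for each outcome with group, time, and group-by-time interaction as fixed effects and a random intercept for subjects". The random part is "a random intercept for subjects with an identity covariance structure". The treatment effect is the interaction: "The group-by-time interactions express the mean outcome change between the 2 trial groups from baseline to posttreatment". No baseline covariate is named, and the arms are not constrained to share a baseline mean.

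The baseline score exists for every primary and secondary outcome. For job-search self-efficacy, for example, "JSSE will be measured at baseline, the postintervention time point, and follow-up". The same section justifies the mixed model by its power when much data is missing, and analyses eligible participants who completed the pretest.

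The Power section gives the planning figure: the G*Power estimate "for a mixed factorial design aiming for a .80 statistical power is 132 participants". It expects about 36% dropout and plans to enrol 180.

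**The concern.** With two time points and a free group term, the interaction contrasts change scores. A change score subtracts the whole baseline value, whereas the posttest regresses on baseline with slope r when the variances are equal, as this model assumes. Subtracting more than the data support adds noise. Regressing on the baseline removes only the predictable part and leaves a smaller residual variance.

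What is at stake is power. The article chose its method for power under heavy dropout, and this parameterisation works against that aim. The information needed to do better is already in the dataset.

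**Working it through.** **The plan's own figures.** The 132 cannot be reproduced, because effect size, alpha and correlation are not given; several unstated combinations come close, so it is neither confirmed nor refuted. The 180 follows from 132 × 1.36 = 179.5. At 36% dropout, 180 × 0.64 = 115 posttests remain.

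**Inputs.** From the article: power 0.80 at 132, enrolment 180, dropout 36%, equal allocation, random intercept with equal variances. Assumed: two-sided alpha 0.05, r from 0.3 to 0.8, all 180 give a pretest, 132 read as complete pairs analysed with the planned interaction test, and missingness that depends only on arm and baseline.

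**Formulas**, with the common factor 4σ² left out, n pretests and c posttests in total:
- Complete pairs, planned model: 2(1−r)/n. Baseline-adjusted: (1−r²)/n. Ratio: (1+r)/2, which is 0.65, 0.75, 0.85 and 0.90 at r = 0.3, 0.5, 0.7 and 0.8.
- With missing posttests, planned model: (1−r²)/c + (1−r)²/n. Baseline-adjusted: (1−r²)/c.

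The second pair applies here. The plan keeps participants who have only a pretest, and they recover part of the loss.

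**Equivalence check.** In simulated complete data the planned model's interaction matched the change-score difference (for example 0.3239 against 0.3239, standard error 0.1461 against 0.1461).

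**Variance and power with n = 180, c = 115.** The reference variance is 2(1−r)/132, set to power 0.80. Power is Φ(2.80 × √(reference/variance) − 1.96).

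| r | Reference | Planned | Adjusted | Ratio | Power, planned | Power, adjusted |
|---|---|---|---|---|---|---|
| 0.3 | 0.01061 | 0.00791 + 0.00272 = 0.01063 | 0.00791 | 0.74 | 0.80 | 0.90 |
| 0.5 | 0.00758 | 0.00652 + 0.00139 = 0.00791 | 0.00652 | 0.82 | 0.78 | 0.855 |
| 0.7 | 0.00455 | 0.00443 + 0.00050 = 0.00493 | 0.00443 | 0.90 | 0.77 | 0.81 |
| 0.8 | 0.00303 | 0.00313 + 0.00022 = 0.00335 | 0.00313 | 0.93 | 0.76 | 0.79 |

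A noncentral F calculation agrees to within about 0.001.

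**With the interim counts in the Results section** (14 of 25 and 28 of 38 observed), at r = 0.5: adjusted 0.75 × (1/14 + 1/28) = 0.0804; extra term for the planned model 0.25 × (1/25 + 1/38) = 0.0166; ratio 0.0804/0.0969 = 0.83. At r = 0.3 and 0.8 the ratios are 0.75 and 0.94.

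**Simulation** (90 per arm, r = 0.5, 36% of posttests missing, true effect 0.4 SD, 300 runs). The free-baseline model had mean standard error 0.179 and rejected in 63% of runs. A common-baseline model, which has the same large-sample variance as covariate adjustment, had 0.162 and 72%. The empirical variance ratio was 0.85, against 0.82 from the formula.

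**The case against.** The planned model is valid and widely used. It is described consistently and fits the mixed factorial design named in the sample size. That stands: this is a matter of precision only. Chance baseline imbalance is random error already reflected in the standard error, not an added bias.

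A reader might infer that randomisation makes the baseline means equal, so that the group term should be dropped at baseline. The documents do not support this. The legend of Figure 2 and the Procedure section put the pretest after randomisation, on the platform for one arm and through an emailed link for the other. Only pretest completers are analysed, 25 against 38 so far out of 130 randomised. Equal means in that subset are not guaranteed. Leaving the group term free is therefore defensible, and only the covariate form of adjustment is recommended.

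A reader might also take the full 25% variance saving at r = 0.5, or a power gain from 0.74 to 0.855 with 115 completers. Those figures treat the planned analysis as change scores on completers only and ignore the baseline-only participants whom the plan includes. The saving at r = 0.5 is about 18%, and the starting power about 0.78.

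The Sociodemographics section says that "participants will fill in their age, gender, residential area, educational level, average monthly income, unemployment period", and one might fault the model for not using these variables. An article commonly leaves the choice of prognostic covariates to a fuller plan, so that is not an error here.

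**Conclusion.** The point holds as an avoidable loss of efficiency in a model that the article states outright. Under the assumptions above, baseline adjustment lowers the variance by about 26% at r = 0.3, falling to 7% at r = 0.8. The power gain falls from about 10 percentage points to about 3.

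The size rests on r, which the documents do not give, and on reading 132 as complete pairs tested by the interaction. At r = 0.8 the adjusted power is 0.79, still under the 0.80 target. It would therefore be wrong to say that adjustment makes up in general for having about 115 posttests and not 132. The planned test is neither biased nor invalid on this account.

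**What to change.** For each outcome, define the primary postintervention (t2) estimate as the between-arm difference at posttest, from a model with arm and that outcome's own baseline score as covariate. Use the covariate form and not a common baseline mean, for the reasons of timing and analysis set given above. Participants with only a pretest add no information to this contrast; the missing-data assumption is still that missingness depends on arm and baseline.

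Keep the planned group-by-time model as a sensitivity analysis. If the arms' pretest completers really differ at baseline, the two analyses can give different answers, and the reader should see both.

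The cost is a change of analysis wording and one degree of freedom per outcome, with no new data collection. Adding covariates collected before randomisation, such as unemployment duration, is optional. The change should be fixed before the final analysis.

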### Specific Objectives

This study aims to investigate the efficacy of iJobs on job-search intensity and effort, the quality of JSBs, and JSSE. We will also assess the employment status and satisfaction with the job (for those who will be employed) 1 month after the intervention. This study will also investigate the effect of iJobs on well-being and mental health.

As a secondary objective, we will evaluate the moderating effects on re-employment of factors such as age, educational level, unemployment period, financial strain, and the mediating effects of job-search intensity, job-search quality, and self-efficacy on re-employment.

Since this is the first large-scale study on a web-based adaptation of the JOBS II program, as stated in the feasibility study [14], we will also evaluate the satisfaction with the intervention, the system usability, and the treatment adherence for the intervention groups.

Specifically, we will test the following hypotheses:

H1: iJobs will increase the job-search intensity (H1a) and job-search effort (H1b) in the intervention group compared to the control group.H2: iJobs will increase the quality of job-search behaviors in the intervention group compared to the control group.H3: iJobs will increase job-search self-efficacy in the intervention group compared to the control group.H4: iJobs will increase self-esteem (H4a), inoculation against setbacks (H4b), and psychological capital (H4c) in the intervention group compared to the control group.H5: iJobs will decrease future career anxiety (FCA; H5a), depression (H5b), anxiety (H5c), and mental health complaints (H5d) in the intervention group compared to the control group.H6: The job-search intensity (H6a), job-search quality (H6b), and JSSE (H6c) will mediate the effect of iJobs on re-employment.H7: Age (H7a), educational level (H7b), unemployment period (H7c), and financial strain (H7d) will moderate the effect of iJobs on re-employment. iJobs will have stronger effects on re-employment for younger participants, participants with higher educational levels, participants with a shorter period of unemployment, and participants with lower levels of financial strain.

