**Assessments^b^**											
	Job-search intensity and effort			✓		✓		✓		✓	
	Job-search quality			✓		✓		✓		✓	
	Job-search self-efficacy			✓		✓		✓		✓	
	Self-esteem			✓		✓					
	Inoculation against setbacks			✓		✓					
	Psychological capital			✓		✓					
	Future career anxiety			✓		✓					
	Depression			✓		✓					
	Anxiety			✓		✓					
	Mental health complaints			✓		✓					
	Physical health	✓									
	Financial strain	✓									
	Sociodemographics	✓									
	Treatment adherence					✓		✓			
	Treatment satisfaction					✓		✓			
	System usability					✓		✓			
	Employment status	✓						✓		✓	
	Job quality (if applicable)							✓		✓	

^a^t0: 2-3 weeks before iJobs; t1: randomization within 1 week before iJobs and pretest assessments for both groups; t2: posttest assessments within 1 week after iJobs for both groups; the control group starts iJobs; t3: follow-up screening 1 month after iJobs for the intervention group; posttest assessments for the control group at the end of iJobs; t4: follow-up screening 1 month after iJobs for the waiting list group.

^b^For a detailed description, see the *Outcomes* section.

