## Results

The enrollment of study participants started in June 2023 and is expected to end in May 2024. Until September 2023, we organized 2 iJobs sessions. Out of the 130 randomized participants, we collected complete data (ie, pre- and postintervention) from 42 participants (*n*_intervention group_=14, *n*_control group_=28). The dropout rate from pretest to posttest in the intervention group was 44% (11/25) and 26% (10/38) in the waiting list control group (see Figure 3 for a flowchart). The data collection is expected to be completed by July 2024. The results are expected to be submitted for publication in the summer of 2024.

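### The efficacy model leaves out baseline factors that the protocol treats as relevant and already schedules before randomisation, so with missing posttests it leans on a narrower missing-at-random assumption than it needs to

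*Protocol article*

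**What the plan says.** The Data Analysis section of the protocol article gives the terms of the model for each outcome: "with group, time, and group-by-time interaction as fixed effects and a random intercept for subjects". It uses data from eligible participants who completed the pretest, does no imputation, and justifies the mixed model by the expected amount of missing data. No baseline factor enters.

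H7, under Specific Objectives, states: "iJobs will have stronger effects on re-employment for younger participants, participants with higher educational levels, participants with a shorter period of unemployment"; lower financial strain is the fourth factor. The Background section says that motivation and search intensity fall as unemployment lengthens, and the Discussion summary says that longer unemployment is worse for well-being.

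Table 1 has rows for "Financial strain" and "Sociodemographics", each with a single tick at t0. Its footnote gives the order: "t0: 2-3 weeks before iJobs; t1: randomization within 1 week before iJobs and pretest assessments for both groups". The Sociodemographics entry is less specific: "At baseline, participants will fill in their age, gender, residential area, educational level, average monthly income, unemployment period, work experience, and targeted professional field".

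The Results section reports: "The dropout rate from pretest to posttest in the intervention group was 44% (11/25) and 26% (10/38) in the waiting list control group".

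**The concern.** A likelihood-based mixed model without imputation is valid under missing-at-random given what is in the model. The article does not name this assumption, but the method implies it. For the baseline-to-posttest comparison, the model contains arm and the outcome's own pretest score.

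Bias in group-by-time needs two things together: an omitted factor must be related to dropout, and it must predict the posttest once arm and pretest are known. Suppose, for example, that people with long unemployment leave the intervention arm more often and also improve less. The observed intervention posttests would then come from a more favourable group, and group-by-time would absorb part of that difference.

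The protocol itself gives reasons to consider such factors and already schedules their collection. Leaving them out gives up an inexpensive way to make the assumption more plausible.

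**Working it through.** **1. Reproduce the dropout figures (Results).** 11/25 = 44.0% and 10/38 = 26.3%, as stated. The difference is 17.7 percentage points. Its standard error is √(0.44×0.56/25 + 0.263×0.737/38) = 0.122, so the 95% interval is 17.7 ± 1.96×12.2, about −6 to 42 points. Fisher's exact p = 0.18. Overall loss from pretest to posttest is 21/63 = 33%.

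**2. Who is in the analysis set.** 25 + 38 = 63 of the 130 randomised had a pretest, and 130 − 63 = 67 did not.

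**3. Size of a possible bias (assumed inputs).** The documents give no association between any factor and dropout or change. Assume one standard normal factor X, oriented so that higher X means more likely completion and more improvement. Let it move the change score by b = 0.2 to 0.3 SD per SD, equally in both arms. Let completion be logistic in X with slope 0.5 or 1.0, calibrated to 56% (intervention) and 74% (control).

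Bias ≈ b × (mean X in intervention completers − mean X in control completers).

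| Slope | Mean X, intervention | Mean X, control (same slope) |
|---|---|---|
| 0.5 | 0.21 | 0.12 |
| 1.0 | 0.36 | 0.22 |

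- X affects completion only in the intervention arm (control mean 0): from 0.2×0.21 = 0.04 to 0.3×0.36 = 0.11 SD.
- X affects completion equally in both arms: from 0.2×(0.21−0.12) = 0.02 to 0.3×(0.36−0.22) = 0.04 SD.

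**4. Does factor plus factor-by-time remove it?** Two-arm, two-time data were simulated with dropout of 44% and 26% and a true effect of zero, and the stated random-intercept model was fitted. Assumptions: X correlated 0.3 with the pretest, pretest-to-posttest slope 0.5, X raising dropout with log-odds 0.7 per SD. Signs are negative because high X now leaves.

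| X drives dropout in | Slope of X on posttest | Bias, stated model | Bias with X and X-by-time |
|---|---|---|---|
| Intervention arm only | 0.2 | −0.054 | −0.001 |
| Intervention arm only | 0.4 | −0.103 | −0.006 |
| Both arms | 0.2 | −0.028 | −0.009 |
| Both arms | 0.4 | −0.044 | −0.003 |

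With dropout unrelated to X, both models gave about −0.01, which is simulation noise.

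**5. What if the factor acts only in the intervention arm, as a moderator would?** Take b = 0.25 in that arm and 0 in control, with completion as in step 3.

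| Selection on X | Slope | Bias, stated model | With X-by-time | Share left |
|---|---|---|---|---|
| Intervention arm only | 0.5 | 0.052 | 0.030 | 58% |
| Intervention arm only | 1.0 | 0.091 | 0.057 | 63% |
| Both arms | 0.5 | 0.052 | 0.043 | 83% |
| Both arms | 1.0 | 0.089 | 0.073 | 82% |

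A common slope therefore leaves roughly 60 to 80% of the bias. Adding centred factor-by-group-by-time terms brings it to about zero.

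**The case against.** The strongest reply is that group, time and group-by-time with a random intercept is a standard analysis for a randomised trial. It contradicts nothing in the article, and adjusted or sensitivity analyses may sit in a fuller plan that is not shown. It stands that the model is conventional. But the article lists the terms, so the point concerns a stated choice and not an absent detail.

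Some stronger readings are tempting and are not supported:

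- **That H7 says these factors shape change in the primary outcomes.** H7 concerns moderation of the effect on re-employment, and says nothing about dropout. The closest statements on the analysed scales concern unemployment duration only (Background and Discussion).
- **That the arms are shown to lose participants at different rates.** The figures are interim, and the interval for the difference includes zero.
- **That the estimate is unbiased only if dropout depends on nothing beyond arm and pretest.** A factor must also predict the outcome given those two before it causes bias.
- **That several factors would add up.** They may overlap or cancel.
- **That t0 collection lets adjustment cover everyone randomised.** The analysis set is pretest completers, and covariates do not bring back the 67 of 130 without a pretest. The timing is also not fully settled: the Sociodemographics entry says only baseline, and the Procedure section places the baseline questionnaire after allocation.

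It also stands that factor-by-time terms alone do not match a moderation rationale, as step 5 shows. The recommendation below takes that into account.

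**Conclusion.** The point holds as a worthwhile improvement to a stated model, not as proof that the planned estimate is biased. The model conditions only on arm and the outcome's own pretest, a third of pretest completers have so far been lost, and the protocol names and schedules factors that could make missing-at-random more credible.

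The size of any bias cannot be derived from the documents. Under the assumed inputs it is about 0.02 to 0.11 SD. The upper end needs selection confined to the intervention arm, and the bias is zero if the factors are unrelated to dropout or to change.

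**What to change.** In Data Analysis, add age, educational level, unemployment period and financial strain, mean-centred, to the mixed model as fixed effects with their interaction with time. Because H7 expects effects to differ by arm, also fit factor-by-group-by-time terms, at least as a prespecified sensitivity analysis. Centring keeps group-by-time interpretable as the effect at the average participant.

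Reconcile the word baseline in the Sociodemographics entry with the t0 tick in Table 1, so that it is clear that these data are recorded before randomisation.

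The cost is a sentence or two of text and a few degrees of freedom. No new data are needed. The change does not address dropout that depends on unobserved posttest values, nor the randomised participants without a pretest.

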## Results

The enrollment of study participants started in June 2023 and is expected to end in May 2024. Until September 2023, we organized 2 iJobs sessions. Out of the 130 randomized participants, we collected complete data (ie, pre- and postintervention) from 42 participants (*n*_intervention group_=14, *n*_control group_=28). The dropout rate from pretest to posttest in the intervention group was 44% (11/25) and 26% (10/38) in the waiting list control group (see Figure 3 for a flowchart). The data collection is expected to be completed by July 2024. The results are expected to be submitted for publication in the summer of 2024.

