**Figure 2 figure2:**
[figure not shown]
Study design and procedure overview. t0: 2-3 weeks before iJobs; t1: randomization within 1 week before iJobs and pretest assessments for both groups; t2: posttest assessments within 1 week after iJobs for both groups; the control group starts now iJobs; t3: follow-up screening 1 month after iJobs for the intervention group; posttest assessments for the control group at the end of iJobs; t4: follow-up screening 1 month after iJobs for the waiting list group.

The participants from the intervention group will receive an email with the iJobs calendar and brief instructions. Afterward, they will receive an email with the platform login information. The username will be a random combination of digits (eg, IJ105) to ensure participants’ anonymity during the program. The account password is generated automatically by the platform. Once participants access their accounts, an introductive module containing the baseline measures questionnaire will be available on the platform. Meanwhile, the waiting list control group participants will receive an email with the iJobs period and a link to the baseline questionnaire.

On the iJobs’ platform, each module will be available for completion for 27 hours. After participants receive personalized written feedback on the platform from the team of counselors involved in the program, the following module will become automatically available for completion. After the last module, the posttest questionnaires will be available on the platform for 48 hours.

Further, 2 weeks after the intervention group finishes iJobs, the control group will start the intervention and go through the abovementioned steps. The questionnaire from the introductive module is the posttest measure for the control group.

Additionally, 1 month after the intervention, the participants who complete the posttest measures will be contacted to complete a brief questionnaire that evaluates their employment status and JSBs.

An overview of this study’s period is presented in Table 1.

**Table 1 table1:** Study timeline. Time points and outcome assessments for the intervention group and waiting list group from enrollment to follow-up.

			Time point^a^								
			Enrollment (t0)		Randomization and pretest measurement (t1)		Posttest measurement (t2)		Follow-up intervention group (t3)		Follow-up control group (t4)
Enrollment			✓								
Eligibility screen			✓								
Informed consent			✓								
Randomization					✓						

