### Limitations

Even if the web-based format of iJobs has some advantages, it also has some limitations. Social support is one of the most critical components of the JOBS II program. In the web-based format, mutual social support between beneficiaries is absent, while the support from the trainers comes only through written feedback messages. Immediate feedback for some types of exercises (eg, practice interviews) might be more valuable for participants. In addition, the solution for substituting social support constrains the participants to stick to specific timeframes while completing iJobs.

Another significant limitation is this study’s design. The waiting list control group also completes iJobs, so we cannot compare the groups regarding employment at the follow-up. The relatively high dropout rate is also a concerning factor. The recruitment strategy should be reconsidered to reduce the number of iJobs sessions taken and simultaneously increase the number of participants who benefit from them. By now, the program has been promoted on social media (ie, Facebook) through paid advertising. For further iJobs sessions, we are considering promoting the program also via web-based newspapers, recruiting agencies, and labor force agencies.

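### Allocation appears to be made session by session, but the written-out model has no session term: a small loss of precision, and no protection if dropout varies by arm and session together

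*Protocol article*

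**What the plan says.** - **Results:** "Until September 2023, we organized 2 iJobs sessions". The same section says "The enrollment of study participants started in June 2023 and is expected to end in May 2024". The total number of sessions is not given.
- **Procedure, Figure 2 legend (and Table 1 footnote):** "t1: randomization within 1 week before iJobs and pretest assessments for both groups". Trial Design gives a 1:1 ratio. Neither blocking nor stratification by session is mentioned.
- **Data Analysis:** each outcome is modelled with "group, time, and group-by-time interaction as fixed effects and a random intercept for subjects", using everyone eligible who has a pretest and no imputation. The term list and the covariance structure are both written out, and session is not among the terms.
- **Results, dropout:** pretest-to-posttest dropout is 11/25 (44%) in the intervention arm and 10/38 (26%) in the control arm, leaving 14 and 28 with both measures. No figure is given by session.
- **Limitations, recruitment:** "By now, the program has been promoted on social media (ie, Facebook) through paid advertising", and "For further iJobs sessions, we are considering promoting the program also via web-based newspapers, recruiting agencies, and labor force agencies".

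**The concern.** If allocation is made afresh before each session, session is a design factor, and a model normally carries the factors within which people were randomised. Everyone in a session follows one calendar, and the job-search behaviour scale looks back two weeks. Season, the local labour market and the recruitment source could therefore shift the pre-to-post change of a whole session, in both arms alike. A subject random intercept cannot remove a shift in change.

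Two things are at stake. One is precision, because unmodelled session-by-time variation goes into the residual. The other is the handling of missing data. The plan relies on the mixed model alone, so dropout must be explained by what the model contains. If both dropout and change depend on session, and dropout does so differently by arm, leaving session out biases the group-by-time estimate.

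**Working it through.** **The plan's own figure.** The 132 for 80% power cannot be re-derived, because effect size, alpha, correlation and test family are not stated. I take 132 (66 per arm) as the analysed number and assume two-sided alpha 0.05 and an effect that gives exactly 80% power.

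**1. Precision, no dropout.** In outcome-SD units, with pre-post correlation ρ, the variance of change is v = 2(1−ρ): 1.0 at ρ = 0.5 and 0.6 at ρ = 0.7. Let τ be the SD of session differences in change (assumed). Omitting session raises the residual variance of change by r = (v + τ²)/v. At 80% power the effect is 1.96 + 0.84 = 2.80 standard errors.

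- *Allocation not balanced within sessions.* The true and reported standard errors both grow, so power = Φ(2.80/√r − 1.96) and type I error stays at 5%.
- *Allocation balanced 1:1 within sessions.* The true standard error is unchanged and only the reported one grows, so power = Φ(2.80 − 1.96√r) and type I error = 2[1 − Φ(1.96√r)].

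| ρ | τ | r | Power, unbalanced | Power, balanced | Type I error, balanced |
|---|---|---|---|---|---|
| 0.5 | 0.1 | 1.010 | 79.6% | 79.7% | 4.9% |
| 0.5 | 0.2 | 1.040 | 78.4% | 78.9% | 4.6% |
| 0.5 | 0.3 | 1.090 | 76.5% | 77.5% | 4.1% |
| 0.7 | 0.1 | 1.017 | 79.3% | 79.5% | 4.8% |
| 0.7 | 0.2 | 1.067 | 77.4% | 78.2% | 4.3% |
| 0.7 | 0.3 | 1.150 | 74.3% | 75.8% | 3.6% |

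Example: ρ = 0.5, τ = 0.3 gives 2.80/√1.09 − 1.96 = 0.72, and Φ(0.72) ≈ 0.765. Session differences in level alone cost nothing: a simulation with balanced sessions gave power 0.806 without and 0.805 with session.

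**2. Bias under dropout.** The stated model was simulated with known variance components: 6 sessions of 34 with a pretest (204 in all), 1:1 within session, ρ = 0.5, control dropout 26%, and no true effect. There were 3,000 replicates, with simulation error about 0.17/√3000 = 0.003 SD. Session effects followed a linear trend over sessions.

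| Intervention dropout | Level SD | τ | Bias without session | Bias with session and session-by-time |
|---|---|---|---|---|
| 44% in every session | 0.3 | 0.2 | 0.002 SD | 0.002 SD |
| 64% falling to 24% | 0.3 | 0 | 0.04 SD | 0.001 SD |
| 64% falling to 24% | 0.3 | 0.2 | 0.09 SD | 0.004 SD |
| 64% falling to 24% | 0 | 0.3 | 0.08 SD | 0.006 SD |

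The second row shows that the intercept's protection against level differences is slightly incomplete once dropout varies by arm and session. The 64%-to-24% pattern is an assumption. The documents give nothing by session.

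**3. Cost of the extra terms.** S sessions add 2(S−1) parameters. At the pace so far, 42/2 = 21 participants with both measures per session, so 132 needs 132/21 ≈ 6 sessions and 10 parameters. With no session effects and balanced allocation, the simulated standard error was 0.166 with and without the terms. If allocation is not balanced within sessions, about (6−1)/(132−1) = 3.8% of the information goes to chance imbalance, and power with the terms is about Φ(2.80 × √0.962 − 1.96) = 78.5%.

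**The case against.** The strongest reply is that the stated model is already a valid randomised comparison. Both arms of a session share the same calendar period, so season and labour market do not bias the contrast. Level differences are taken up by the subject intercept. Omitting session does not inflate type I error. Covariates are often left to an analysis plan, which is not shown here. Most of this stands, and it is why the point is small. The last part does not fully answer it, because the article lists its fixed effects and its covariance structure, and session is not among them.

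The net gain can also vanish. If allocation is not balanced within sessions, adjustment recovers about 78.5% power rather than 80%, so at ρ = 0.5 it only breaks even near τ = 0.2.

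A reader might infer from 14 versus 28 participants with complete data that session already confounds the comparison. The documents do not support that. These are totals pooled over sessions; with the same 1:2 ratio in each session, session could not confound at all. A bias can be constructed, for example 0.3 × (10/14 − 12/28) = 0.086 SD, but both the 0.3 SD difference and the split by session would be invented. That sum also treats the analysis as completers only, whereas the model keeps everyone with a pretest.

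Nor do the documents say that the recruitment channel will change. The Limitations section says that further channels are being considered in addition, and the sections on recruitment and procedure already list newspapers and agencies.

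**Conclusion.** The point holds as a modest improvement. Session-wise allocation is an inference from the Figure 2 legend, but a fair one, and the model as written ignores session. For an assumed session-by-time SD up to 0.3, the loss is at most about 4 power points at correlation 0.5 and 6 at 0.7. It is about one point less if allocation is balanced within sessions, in which case the test is also conservative. Bias is about zero unless dropout differs by arm and session together; under one assumed pattern of that kind, with τ up to 0.3, it was 0.04 to 0.09 SD. The documents show dropout differing by arm and are silent on session, so this is a possibility to guard against, not a demonstrated bias. Every size given here depends on assumed session effects and correlations.

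**What to change.** Add session and session-by-time as fixed effects to each primary and secondary outcome model, including the baseline-to-follow-up comparisons. Keep the single group-by-time coefficient as the reported effect. Without a group-by-time-by-session term there is one common effect and nothing to average over sessions. Report pretest completion and dropout by session and arm, so that readers can see whether the condition for bias occurred. State whether the 1:1 allocation is balanced within sessions; balancing it in the remaining ones would make the adjustment nearly free.

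The cost is two extra parameters per session beyond the first. So far there are 14/2 = 7 intervention participants with both measures per session, so very small sessions may need pooling with a neighbour. Write down the pooling rule and the model before outcomes are compared by arm. No new data are needed beyond each participant's session.
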